## Abstract

Background: Chronic tinnitus can have an immense impact on quality of life. Despite recent treatment advances, many tinnitus patients remain refractory to them. Preclinical and clinical evidence suggests that deep brain stimulation (DBS) is a promising treatment to suppress tinnitus. In rats, it has been shown in multiple regions of the auditory pathway that DBS can have an alleviating effect on tinnitus. The thalamic medial geniculate body (MGB) takes a key position in the tinnitus network, shows pathophysiological hallmarks of tinnitus, and is readily accessible using stereotaxy. Here, a protocol is described to evaluate the safety and test the therapeutic effects of DBS in the MGB in severe tinnitus sufferers. Methods: Bilateral DBS of the MGB will be applied in a future study in six patients with severe and refractory tinnitus. A double-blinded, randomized 2 × 2 crossover design (stimulation ON and OFF) will be applied, followed by a period of six months of open-label follow-up. The primary focus is to assess safety and feasibility (acceptability). Secondary outcomes assess a potential treatment effect and include tinnitus severity measured by the Tinnitus Functional Index (TFI), tinnitus loudness and distress, hearing, cognitive and psychological functions, quality of life, and neurophysiological characteristics. Discussion: This protocol carefully balances risks and benefits and takes ethical considerations into account. This study will explore the safety and feasibility of DBS in severe refractory tinnitus, through extensive assessment of clinical and neurophysiological outcome measures. Additionally, important insights into the underlying mechanism of tinnitus and hearing function might be revealed. Trial registration: ClinicalTrials.gov NCT03976908 (6 June 2019).

## 1. Introduction

Tinnitus, commonly known as “ringing of the ears”, is one of the largest health challenges in the world [1]. According to a recent large survey, approximately 6.4% of Americans experience persistent tinnitus [2]. One in ten patients experiences the most extreme and debilitating form of tinnitus. Sleep deprivation, anxiety, and depression often accompany tinnitus and severely affect the patient’s quality of life [3,4,5]. In turn, this places a huge burden on society, and healthcare costs, and decreases productivity [6]. 

Subjective tinnitus has a multifactorial origin with heterogeneous patient profiles, which makes it a highly complex condition. The absence of an underlying medical cause in most cases leaves many patients without an available curative evidence-based treatment [7,8]. Tinnitus combined with sensorineural hearing loss might benefit from hearing aids. However, somewhere between 22% and 80% of affected patients are adequately served by using hearing aids [9,10]. The current clinical practice primarily aims at reducing the impact of tinnitus by providing psychoeducation and improving coping strategies via various psychological interventions [11,12]. 

The etiological and pathophysiological mechanisms of subjective tinnitus are complex and not fully understood. Many investigators feel that in nearly all tinnitus cases, there is some degree of cochlear impairment, leading to diminished auditory nerve activity reaching the cochlear nuclei [13]. Much evidence implicates the head and neck somatosensory system as a separate major factor in the development of tinnitus. It is likely that most tinnitus develops as a result of interactions between these two systems within the central nervous system [14]. According to current theories, tinnitus is associated with increased neural activity in auditory cortices, possibly resulting from maladaptive gating [15,16] and/or an increase in central gain [17]. Specific neural correlates described in tinnitus models are enhanced neuronal synchrony, increased spontaneous firing, and changes in tonotopic organization [18]. 

A commonly applied neuromodulation technique is deep brain stimulation (DBS). This therapy has been widely used in neurologic and neuropsychiatric disorders such as Parkinson’s disease. DBS is generally applied using high-frequency stimulation (>100 Hz), to disrupt pathological neuronal activity and oscillations [19,20]. Hypothetically, this results in an alteration of tinnitus perception and related distress. Further, patients treated with DBS for a movement disorder sometimes also suffered from tinnitus. DBS of non-auditory structures in these patients led to diminished or completely suppressed tinnitus [21,22,23,24,25,26,27]. Other implants that could potentially influence tinnitus, and have been investigated, are a cochlear implant (CI) [28] and an auditory brainstem implant (ABI) [29], however, these can only be used in patients with severe hearing loss. In addition, other neuromodulation techniques, such as vagal nerve stimulation [30] and cortical stimulation [31], have been investigated with various degrees of success. These latter treatments can also be used in patients without hearing loss, however, at the moment, there is insufficient evidence to implement these treatments in clinical practice. For a comprehensive review of neuromodulation for tinnitus, see Deklerck et al. [32]. Our hypothesis is that influencing the pathological tinnitus network at any level could be beneficial in theory, but the site at which stimulation is performed strongly influences the outcome. Stimulation in close proximity to the site at which the pathological activity is generated, i.e., within the brainstem [33], might be a more direct and thus efficient target. This could also explain why non-invasive cortical stimulation fails to show conclusive favorable outcomes [34,35].

Preclinically, at multiple levels of the central auditory pathway from cochlear nuclei to the auditory cortex, tinnitus-related neuronal activity is similar to subthalamic nucleus activity in Parkinson’s disease, i.e., enhanced spontaneous activity and burst firing [36,37,38,39]. The primary role of auditory thalamic neurons is to actively and dynamically shape neural representations of information and to control which information reaches the cerebral cortex [40].

Moreover, preclinical studies support the beneficial effects of DBS on tinnitus when applied in auditory brain areas [21,22,23,24,25,26,27]. In Table 1 we listed all currently available animal and human studies that applied DBS for tinnitus. In our lab a rat model for tinnitus was used in order to test DBS as a potential treatment for tinnitus. Noise exposure was used to induce tinnitus in rats after which a gap-prepulse inhibition of the acoustic startle reflex (GPIAS) also known as a gap detection task [41] established the presence of tinnitus. This task exploits the acoustic startle reflex which is present in all mammals and consists of a contraction of the major muscles in response to an unexpected loud noise [42]. A reduction in tinnitus-like behavior was shown when DBS was applied in several structures along the classical auditory pathway, including the dorsal cochlear nucleus [43,44,45], inferior colliculus [46], and medial geniculate body (MGB) [47]. Importantly, no undesired side effects occurred. DBS of the MGB did not lead to anxiety or disturbed locomotor activity. DBS of the inferior colliculi did not cause any detectable hearing impairment [48]. Other groups also showed beneficial effects in tinnitus behavior in animal rat models, in the caudate [45] and the dorsal cochlear nucleus [44,45]. A similar setup was used as in our studies. These results also indicate that (high-frequency) stimulation anywhere within the pathological tinnitus network could have a beneficial effect on tinnitus [49,50,51]. 

The MGB is a preferred target area as opposed to other auditory subcortical structures [50], as the auditory thalamus is readily accessible in stereotactic surgery. Consequently, targeting the auditory thalamus bears smaller surgical risks and complications such as bleeding and potential neurological deficit. The MGB of the thalamus is a major relay and gateway between the midbrain and cortex, and a core structure in tinnitus pathophysiology [52,53]. Furthermore, the integration of auditory and limbic information occurs within the MGB [54]. Connected limbic structures, such as the amygdala and nucleus accumbens, are related to emotional and attentional symptoms of tinnitus [55]. Hence, the MGB acts as a central hub in networks involved in tinnitus, which makes it a promising structure for neuromodulatory approaches. 

Currently, MGB DBS has not been applied in humans. The majority of patients with tinnitus can be treated with non-invasive methods, and only a small number of patients can be considered a candidate for DBS. Based on our pre-clinical findings in rat studies, we developed this protocol for a human pilot study.

The primary objective of the proposed study is to assess the safety and feasibility (acceptability) of bilateral MGB DBS in severe tinnitus. Patients with severe tinnitus who are refractory to the standard treatment program will be included. Secondary outcomes will provide data on the potential efficacy of MGB DBS on tinnitus severity (Tinnitus Functional Index (TFI)), tinnitus loudness, and distress (Visual Analogue Scales (VAS)). Additionally, hearing (audiometry), cognition (neuropsychological test battery), quality of life, and psychological functioning (questionnaires) will be assessed. Furthermore, electrophysiological data will assess fundamental aspects of auditory function and tinnitus pathophysiology. After a successful evaluation of the primary and secondary outcomes in this pilot study, MGB DBS could potentially be further developed as a novel treatment option in severe, refractory tinnitus.

## 2. Methods 

### 2.1. Study Design

This pilot study uses a double-blind 2 × 2 crossover design in which MGB DBS will be compared to no stimulation (Figure 1).

### 2.2. Setting

This study will be carried out at Maastricht University Medical Center (MUMC+) in Maastricht, the Netherlands. MUMC+ is an expertise center for tinnitus, providing integrated multidisciplinary diagnostics and rehabilitation for a wide range of tinnitus patients. The Ear, Nose, and Throat department has long-standing clinical expertise and experience with developing neuromodulative therapies for tinnitus such as intracochlear devices [56]. The neurosurgery department has substantial clinical and preclinical expertise in DBS. In addition to a preclinical DBS research line [57], it is well equipped to conduct clinical trials for new indications of DBS therapy such as Gilles de la Tourette syndrome [58]. Acquisition of neurophysiological data, both intra- and postoperatively is standard practice and is used to unravel neural mechanisms [59]. 

The study will be conducted according to the principles of the Declaration of Helsinki (Version 10, 2013) and in accordance with the Medical Research Involving Human Subjects Act (in Dutch: ‘Wet medisch-wetenschappelijk onderzoek met mensen’ (WMO)). This study complied with the CONsolidated Standards Of Reporting Trials (CONSORT) extension statement. Ethics approval was obtained by the institutional review board. Results will be published in an international peer-reviewed scientific journal and presented at scientific meetings.

### 2.3. Recruitment and Consent

Patients are eligible to enroll if they meet the inclusion and none of the exclusion criteria as outlined in Table 1. All patients will be evaluated and selected by a multidisciplinary team of specialists (otolaryngologists, audiologists, neurosurgeons, neurologists, psychiatrists and psychologists). Diagnostics and treatment are in accordance with national tinnitus guidelines [60]. Based on the Dutch tinnitus guidelines, the tinnitus questionnaire (TQ) is used to determine tinnitus severity [61]. Patients suffer severely (TQ score ≥ 47), and are refractory to available treatments including cognitive behavioral therapy and hearing aids in case of hearing loss.

Patients will be recruited at the outpatient clinic of the Ear Nose Throat department. If patients give permission, they receive an information brochure. Two weeks after, researchers will contact the patients to plan a face-to-face meeting. During this meeting, a full understanding of the study protocol is ensured and additional questions are answered. When a patient needs more time to decide, the investigator plans a follow-up appointment after a few weeks. If a patient agrees to participate in the study, informed consent will be signed by the patient and investigator. If the patient meets the criteria, a second outpatient visit will be planned. During this visit, an intake interview will be conducted by one of the researchers, followed by a consultation with both a psychiatrist and a neurosurgeon. Then, the multidisciplinary team will form a collective decision on inclusion or exclusion. Following a positive decision of the multidisciplinary team, a standard clinical workup for DBS surgery will follow. This includes conducting a brain scan and general blood examination. If inclusion criteria are still met, final inclusion will follow. Patients can leave the study at any time for any reason without any consequences. The investigators can decide to withdraw a subject from the study for urgent medical reasons. 

### 2.4. Outcomes

The time frame and methods of data acquisition are displayed in Figure 1 and Table 2, respectively.

#### 2.4.1. Primary Outcomes

The primary focus of this pilot study is to assess safety and feasibility. Safety will be assessed by reporting the rate and grade of all surgical and stimulation induced adverse events in the study sample during the study period. Feasibility will be assessed in terms of the acceptability of the intervention, by taking qualitative interviews at all major time points (T0, T1, T2, T3; see Table 3), and by comparing satisfaction during sham stimulation and DBS. 

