### 3.4. Randomization and Blinding

Randomization will be performed directly after the period of stimulation optimization by an independent institution, the Clinical Trial Center Maastricht (CTCM). Patients will be randomly assigned to one of the two study groups. The investigator who adjusts DBS parameters cannot be blinded. All other investigators and the patient are blinded to the study group. In case the patients are considered unblinded due to the nature of the stimulation the protocol will be carried out as planned. Only in the case of medical concerns, the patient and investigators will be unblinded in order to provide the care needed.

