### 3.6. Statistical Analyses

The safety and feasibility outcomes will be reported descriptively. Descriptive statistics with 95% confidence intervals will be used to present preliminary data of secondary outcomes such as tinnitus (severity, loudness and distress), anxiety, depression, hearing function, quality of life, and cognitive functioning. These data will provide some insight into population characteristics and might indicate potential changes in mean scores between the intervention and sham stimulation.

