## 4. Discussion

One of the main ethical considerations in this study is balancing risks and benefits. The potential benefit of the intervention is a reduction of tinnitus loudness and tinnitus burden. Risks of this minimally invasive and reversible form of functional neurosurgery are surgery-related complications (e.g., cerebral hemorrhage or infarction, CSF leak, seizures, meningitis or encephalitis), hardware failure (e.g., lead rupture, extension fibrosis, device migration) and stimulation related side effects. These latter effects are unknown as clinical MGB DBS has not been performed before. The function of the MGB is primarily hearing thus other side effects than hearing-related effects are less likely. Animal studies did not show hearing loss, anxiety or locomotion-related side effects in DBS in subcortical auditory structures [43,47,48]. We also reviewed possible side effects based on the brain structures surrounding the MGB. The MGB is located posterior to the subthalamic nucleus. The MGB is 8mm wide, 6mm long and 6.5mm high with its largest volume at -3.5mm from the AC-PC (anterior commissure-posterior commissure) plane. Considering the relatively large size of the MGB, current spread outside the MGB is unlikely if the DBS electrode is positioned in the center. Neighboring structures of the MGB are structures similar to other commonly used stimulation targets. The current spread to the anterior side of the MGB could result in internal capsule effects. These side effects are known from subthalamic nucleus (STN) DBS treatment for dystonia and Parkinson’s disease. The possible side effects of internal capsule stimulation are dysarthria, muscle contractions, and gaze paresis. Posterior to the MGB the ventricle can be found. Possible side effects are known from anterior nucleus of the thalamus (ANT) DBS which has also a border at the ventricle. Antero-medially the sensory thalamus is located which is targeted when performing DBS to treat pain. More medially the fields of Forel are located. Possible side effects are known from STN DBS in which current spread also may occur to the fields of Forel which can result in disturbances of speech, postural stability and gait. Laterally to the MGB the optic tract is located. We know from globus pallidus internus (GPi) DBS that stimulation of the optic tract elicits phosphenes. All these side effects from current spread to surrounding regions are elicited by stimulation and thus reversible. Taking this together, MGB DBS could induce changes in auditory sensation, and there is a slight risk for side effects due to current spread. In case of undesired side effects, stimulation parameters can be adapted or stimulation can be turned off. The principal investigator will immediately inform the data safety monitoring board and the medical ethical committee in case of serious side effect. 

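### As worded, the primary safety outcome counts only surgical and stimulation-induced events, so hardware events and events of uncertain cause fall outside it

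*Protocol article*

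**What the plan says.** Section 2.4.1 makes safety one of the two primary outcomes, assessed by "reporting the rate and grade of all surgical and stimulation induced adverse events in the study sample during the study period". Section 3.6 adds only this: "The safety and feasibility outcomes will be reported descriptively". It names no wider set of events.

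Section 4 sets out the risks in three classes. The first is "surgery-related complications (e.g., cerebral hemorrhage or infarction, CSF leak, seizures, meningitis or encephalitis"; the other two are "hardware failure (e.g., lead rupture, extension fibrosis, device migration) and stimulation related side effects". On the third class it adds: "These latter effects are unknown as clinical MGB DBS has not been performed before". The Introduction confirms the first-in-human status: "Currently, MGB DBS has not been applied in humans".

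Section 3.7 fixes the sample at six patients without replacement. Table 3 runs from inclusion through surgery, recovery, optimisation and two 6-week randomised periods to a third period of 6 months with stimulation ON.

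**The concern.** The outcome takes up two of the three risk classes that the article itself names. The word *all* in Section 2.4.1 does not help, because it works only inside the two causes that follow it.

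The wording also makes attribution a condition of entry: an event must first be judged surgical or stimulation induced. That judgement is hardest to make in this study, because there is no earlier human experience of the target to judge against. Section 4 also expects effects other than hearing-related ones to be less likely. An unexpected event of another kind could therefore easily be judged unrelated, and it is what a first-in-human study most needs to show.

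Safety is the primary question. The Introduction ties further development to a successful evaluation of the outcomes, and Section 2.4.2 allows future procedures to be adapted, or terminated in case of adverse events. A primary table that lacks one class of device harm and all unresolved events is a poorer basis for those decisions.

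**Working it through.** The article gives no event rate, threshold or sample-size calculation for safety, so there is no figure of its own to reproduce. The check compares wording, followed by an illustration of size.

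**Step 1. Risk classes in Section 4 against the outcome in Section 2.4.1.**

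| Kind of event | Named as a risk in Section 4 | Counted under Section 2.4.1 as worded |
|---|---|---|
| Surgery-related | yes | yes |
| Hardware failure | yes, as its own class | not named |
| Stimulation-related | yes, effects unknown | yes, if judged induced by stimulation |
| Cause undetermined | not a class | no, since neither cause is established |

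**Step 2. Does another part of the article bring the missing rows back?** Section 3.6 does not widen the set. No section says that events are reported whatever their cause, that hardware events count as surgical, or how an event of uncertain cause is handled.

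**Step 3. Direction.** A count restricted by cause can never exceed the all-cause count from the same patients. Against an all-cause count, the omission can therefore only lower the figure.

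**Step 4. Size for one or two omitted patients.** Inputs: n = 6 (Section 3.7) and x = number of patients with an event. The exact (Clopper-Pearson) 95% limits are:

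- lower = the 2.5% quantile of Beta(x, n − x + 1), or 0 when x = 0
- upper = the 97.5% quantile of Beta(x + 1, n − x)

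| x | x/6 | Exact 95% CI |
|---|---|---|
| 0 | 0% | 0 to 45.9% |
| 1 | 16.7% | 0.4 to 64.1% |
| 2 | 33.3% | 4.3 to 77.7% |

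By hand for two of the limits: with x = 0, upper = 1 − 0.025^(1/6) = 0.459; with x = 1, lower = 1 − 0.975^(1/6) = 0.004.

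If the only affected patient has a hardware or undetermined event, the primary result reads 0/6 where the all-cause result is 1/6. With two such patients it reads 0/6 where the all-cause result is 2/6.

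**Step 5. How likely is such a case?** The article gives no hardware event rate, so the per-patient risk p below is an assumption shown over a range. The chance of at least one affected patient in six is 1 − (1 − p)^6.

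| Assumed p | Chance of at least one in six |
|---|---|
| 5% | 26% |
| 10% | 47% |
| 20% | 74% |
| 30% | 88% |

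**The case against.** The strongest case on the other side has five parts.

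- **Surgical may include hardware.** Section 3.1 treats the placing of electrodes and pulse generator as a two-stage operation, so a migrated or ruptured lead could be called a surgical complication. No sentence excludes hardware events. This reading is possible, but Section 4 gives surgery its own examples and lists hardware separately. It also does nothing for events of uncertain cause.
- **The article is a condensed text.** Definitions, collection rules and causality rules for adverse events are commonly left to the full protocol. This stands, and it means that nobody can say from the article that such events go unrecorded. The article does, however, state the outcome definition, and the point concerns that definition.
- **The monitoring board sees safety data (Section 3.5).** This stands as oversight, but board review is not the reported primary outcome.
- **Hearing, mood, cognition and quality of life are measured in all patients whatever the cause** (Section 2.4.2, Table 3) and reported with 95% confidence intervals (Section 3.6). This stands and limits the loss in those domains. These are secondary outcomes at set visits, and they do not capture hardware events.
- **No formal decision hangs on the figure.** There is no threshold, test or numerical stopping rule for safety. This also stands: the shift in Step 4 alters what readers see, not a stated decision rule.

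Two stronger readings go beyond the text.

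A reader might infer that most follow-up is ON time, so attribution by timing would distort the result. No section says that attribution is made by timing. Any split of ON and OFF time needs assumptions about the length and state of optimisation and about surgery and recovery. Attribution by timing would also tend to add unrelated events to the stimulation class, which is the opposite of leaving events out.

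A reader might also infer that cause is judged unblinded, because "The investigator who adjusts DBS parameters cannot be blinded". The same section keeps the other investigators and the patient blinded, and nothing gives the causality judgement to the person who adjusts the settings.

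**Conclusion.** The point holds as a fault in a stated definition. Followed as worded, Section 2.4.1 leaves hardware events and events of undetermined cause out of the primary safety result, although Section 4 names hardware failure as a risk of its own and calls the stimulation effects unknown.

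One omitted patient is worth 1/6, or 16.7 percentage points, and turns an interval of 0.4 to 64.1% into one of 0 to 45.9%. Both intervals are wide, so the main harm is that a primary table could show no affected patient when there was one.

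The conclusion rests on taking surgical in the sense that Section 4 gives it. It does not rest on any assumed hardware rate; the range in Step 5 only shows that such a case need not be remote. It does not extend to saying that the events are lost to the study, that cause is judged unblinded, or that the rate of stimulation-caused harm is biased in a known direction.

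**What to change.** Reword Section 2.4.1, and Section 3.6 to match, along these lines: the number, grade and seriousness of all adverse events, whatever the cause, in every patient who starts surgery, through the end of Period III.

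- Give each event a cause class: surgical, hardware, stimulation, unrelated or undetermined. The class describes the event and does not decide whether it is counted.
- Tabulate events by study phase, with the randomised ON and OFF periods side by side. Those two 6-week periods are the randomised comparison for stimulation.
- Use patients who start surgery as the base. Section 3.4 places randomisation after optimisation, so a base of randomised patients could miss someone harmed before that point.

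The change touches no treatment, visit or sample size. It costs a few lines of text, one classification column and a longer event list with some unrelated events in it. If the full protocol already records all adverse events, only the reporting changes.
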